### Demographics and baseline characteristics

Comparability at baseline (of the 1st episode) between the two treatment groups will be assessed on the safety, ITT and PP populations for demographics and baseline characteristics.

The medical history / concomitant diseases (coded using system organ MedDRA) will be compared by group of treatment at the randomization time and described for the following attacks.

Concomitants treatments (coded using the WHO Drug Dictionary (ATC Code)) will be compared by group of treatment and described for the following attacks.

### Extent of study treatment exposure and compliance

The analysis of the compliance will be performed on the safety population and on the ITT population.

Number of tablets taken

Compliance = ---------------------------------------------------------------------------- x 100

theoretical Total number of tablets taken

The compliance will be calculated for each attack.

The evolution of the compliance will be analyzed for each patient during the 2 years of follow-up.

The mean compliance will be presented by group of treatment and overall.

An exploratory analysis could be performed by dosing blood level of DSAQ or Lumefantrine on D3.

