# Treatments

## Investigational Product

### Coarsucam® (artesunate+amodiaquine fixed-dose combination)

Coarsucam® double-layer artesunate/amodiaquine tablets (from Sanofi-aventis); 2 homothetic dosage strengths:

- Infants tablets: AS 25/AQ 67,5 mg
- Toddlers tablets: AS 50/AQ 135 mg
- Children tablets: AS 100/AQ 270 mg

The dosages of Coarsucam® are adapted according to the patient’s body weight:

Body weight ≥5 and <9 kg: daily dosage of 25/67.5mg.

Body weight ≥9 and <18 kg: daily dosage of 50/135 mg*.*

Body weight ≥18 and <36 kg: daily dosage of 100/270 mg*.*

Body weight ≥36 kg: daily dosage of 200/540 mg*.*

Coarsucam® is administered in 1 intake per day.

The treatment duration is 3 days.

The tablets are administered orally with a small amount of still drinking water. For the younger children, the tablets may be dissolved and administered with still drinking water.

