### Coartem®  (artemether+lumefantrine):

The artemether/lumefantrine fixed-dose combination tablets (from Novartis) contain 20/120 mg.

The dosages of Coartem® are adapted according to the patient’s body weight:

Body weight <15 kg: daily dosage of 40/240mg in 2 intakes

Body weight ≥15 and <25kg: daily dosage of 80/480mg in 2 intakes

Body weight ≥25 and <35kg: daily dosage of 120/720mg in 2 intakes

Body weight ≥35 daily dosage of 160/960mg in 2 intakes

An interval of at least 8 hours must be maintained between the 1st and the 2nd intake (1st day).

The treatment duration is 3 days.

The tablets are administered orally with still drinking water. Food or milky drink should be taken as soon as possible after each intake.

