## Packaging and labeling

All test drugs (investigational products- IPs) will be stored in their original packaging in the study clinic.Commercial blister packs of 3 tablets for Coarsucam® and 8 tablets for Coartem® will be used. A label with the study reference, patient number (to be filled in) and the statement “product for use in clinical trials” will be affixed to each blister/pack.

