## Treatment accountability and compliance

For the first attack, each dose of the study treatment will be administered by a study nurse, and the patient will be monitored for 30 minutes after administration. If the patient vomits or rejects the treatment within the 30 minutes, the same dose will be re-administered. In the event of repeated vomiting, a replacement treatment will be given as discussed in 9.7.3. Study participants may choose to either be hospitalised (retained at the clinic) for administration of study medications or to commute from home. Participants will be reimbursed for transport to and from the clinic and for meals or other incidental expenses if they are hospitalised for treatment administration. Amounts for reimbursement will be based on the current rates for transport, meals and incidental expenses. Home visitors shall actively follow patients who do not come for scheduled appointments.

For the repeat attacks the 1st intake will be administered at the study clinic and the other intakes will be unsupervised. At day 3, the patient will give the blister to the study nurse who will check the number of remaining tablets in the returned blister. The parent/guardian will inform the clinical team member of any event related to these intakes. In case of vomiting of an unsupervised intake within the 30 minutes, the patient will visit the study clinic where the same dosage will be administered again.

The study nurse shall record the information on the appropriate CRF page. The Monitor in charge of the study then checks the CRF data by comparing them with the Investigational Product which he/she has retrieved and treatment log forms. All steps will be taken to ensure that patients receive treatment in compliance with the protocol.

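### The compliance formula counts clinic-given doses, a larger share of the course on Coarsucam than on Coartem, so it does not measure the unsupervised adherence that the objective compares

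*Protocol*

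**What the plan says.** Section 14.5.2 gives compliance as a ratio times 100. The numerator is "Number of tablets taken" and the denominator is "theoretical Total number of tablets taken". It adds that "The compliance will be calculated for each attack", that its change over the two years will be analysed for each patient, and that "The mean compliance will be presented by group of treatment and overall". Nothing removes doses given by staff, and nothing leaves out the first attack.

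Section 9.9 has a study nurse give every dose in the first attack. After that the arrangement changes: "For the repeat attacks the 1st intake will be administered at the study clinic and the other intakes will be unsupervised". Section 9.1 sets the regimens: "Coarsucam® is administered in 1 intake per day" for 3 days, while Coartem is given in two intakes a day for 3 days, which section 5.3 counts as six doses.

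The synopsis and section 6.2 list compliance as a between-arm comparison for repeat attacks only. Section 10.3 is likewise confined to the second and later attacks and uses the count of tablets left at D3. On packs, section 9.3 says: "Commercial blister packs of 3 tablets for Coarsucam® and 8 tablets for Coartem® will be used".

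**The concern.** The objective asks how well families give treatment at home. The formula mixes that with doses that staff gave, and the staff-given part differs by arm because one regimen has three intakes and the other six. Part of any difference in reported compliance would then come from the number of intakes, not from behaviour. Section 5.4 makes compliance under unsupervised intake one of the things the trial is to validate, so the measure should isolate it.

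The first attack adds a second problem. Its values should lie near 100% in both arms by design. If they enter the group mean they dilute any arm difference. If they start the two-year trend, the step from attack 1 to attack 2 mixes a change in supervision with a change in adherence.

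**Working it through.** The protocol states no compliance figure, so there is none to reproduce. The check is arithmetic on its formula.

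**Supervised share of a repeat attack (sections 9.1 and 9.9).** Coarsucam: 3 intakes, the first at the clinic, so 1/3; the share is the same in every weight band (1 of 3 tablets, or 2 of 6). Coartem: 6 intakes, the first at the clinic, so 1/6 in every weight band (1/6, 2/12, 3/18 or 4/24 tablets).

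**Formula.** With supervised share s, and p the share of home tablets taken, compliance = s + (1 − s)p. This is 1/3 + 2p/3 on Coarsucam and 1/6 + 5p/6 on Coartem. With the same p in both arms the gap is 1/6 − p/6 = (1 − p)/6.

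| p (assumed, both arms) | Coarsucam | Coartem | Gap, points |
|---|---|---|---|
| 100% | 100.0% | 100.0% | 0 |
| 95% | 96.7% | 95.8% | 0.8 |
| 90% | 93.3% | 91.7% | 1.7 |
| 80% | 86.7% | 83.3% | 3.3 |
| 70% | 80.0% | 75.0% | 5.0 |
| 50% | 66.7% | 58.3% | 8.3 |
| 0% | 33.3% | 16.7% | 16.7 |

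**Other meanings of equal adherence.** An equal share of home tablets is one definition among several. Patterns counted in days or intakes give:

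| Pattern in both arms | Protocol formula, Coarsucam v Coartem | Home tablets only, Coarsucam v Coartem |
|---|---|---|
| Stop after day 1 | 1/3 v 2/6: 33.3% each | 0/2 v 1/5: 0% v 20% |
| Stop after day 2 | 2/3 v 4/6: 66.7% each | 1/2 v 3/5: 50% v 60% |
| Miss one home intake | 2/3 v 5/6: 66.7% v 83.3% | 1/2 v 4/5: 50% v 80% |

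The formula is therefore neutral when families stop on the same day. With one missed intake it favours Coartem, but shows 16.7 points where the home shares differ by 30.

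**General case.** With home shares a (Coarsucam) and b (Coartem), the displayed gap minus a − b is (1/6 + 2a/3 − 5b/6) − (a − b) = (1 − 2a + b)/6. This is positive, in favour of Coarsucam, when a < (1 + b)/2, and negative when a is larger.

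**Attack 1.** Suppose a child's k attacks are averaged with equal weight and attack 1 scores 100% in both arms. The arm difference then shrinks by the factor (k − 1)/k, for example by half at k = 2. Both the averaging and k are assumptions.

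**Packs.** Section 9.1 uses Coartem tablets of 20/120 mg, and its lowest band reads: "Body weight <15 kg: daily dosage of 40/240mg in 2 intakes". In tablets per course: 40/20 × 3 = 6; 80/20 × 3 = 12; 120/20 × 3 = 18; 160/20 × 3 = 24. No course is 8 tablets, and only 24 is a whole number of 8-tablet blisters. A fully adherent child on the 6-tablet course who is handed one full blister returns 2 tablets.

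**The case against.** The strongest objection is that the full-course ratio is a legitimate measure of exposure, and that section 14.5.2 covers exposure as well as compliance. That stands, and it is a reason to keep the ratio for that purpose. It does not make the ratio a measure of unsupervised adherence.

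Next, the direction. A reader might infer that the formula always favours Coarsucam. It does not: the advantage appears when both arms take the same share of home tablets, and disappears or reverses under the day-based and intake-based patterns above. A home-only share is also not neutral, since one missed intake costs 1 of 2 on Coarsucam and 1 of 5 on Coartem. The choice between them is about which question is answered, and the objective asks about home intake.

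The size can be small. At p of 90% or more the gap is at most 1.7 points, and the largest figures need half or none of the home doses to be taken. Section 14.5.2 only presents means, and compliance is not in the list of comparisons in section 14.5.3.2. That limits the consequence, although section 6.2 still calls for a comparison.

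On attack 1, the protocol does not say that attacks are pooled; by group and overall may simply mean each arm and both together. The point is only that attack 1 is not excluded, while the objective and section 10.3 cover later attacks.

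Two further readings are not supported. One is that a fully adherent 6-tablet Coartem course scores 6/8 = 75%: the denominator is the theoretical total, so 6 taken gives 6/6 = 100%, and section 10.3 requires discordant counts to be queried. The other is that once-daily dosing is the stated compliance rationale for Coarsucam. Section 5.2 cites avoiding intake of only one of the two drugs and having fewer tablets; the adherence concern over twice-daily intake is a remark on the comparator in section 5.3.

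The SAP is not at hand and may narrow the calculation. The protocol's explicit formula does not, and section 14.1 makes it the basis of the SAP.

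**Conclusion.** The point holds as a mismatch between measure and objective. The formula counts supervised doses amounting to 1/3 of the course on Coarsucam and 1/6 on Coartem in repeat attacks, and all doses in attack 1. The shares follow from the protocol's own text. The resulting gap of (1 − p)/6 rests on two assumptions: an equal share of home tablets in the two arms, and a value of p that the protocol does not give. Under other patterns the formula is equal between arms or masks part of a home-adherence difference in favour of Coartem. It should therefore be described as blurring the comparison, not as a fixed bias towards one product.

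The pack mismatch is a separate clarification for reading residual counts and does not alter the formula. This is a minor secondary-endpoint issue. The primary analysis uses fully supervised first attacks and is untouched.

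**What to change.** In section 14.5.2:

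- Keep tablets taken over the full course as a measure of exposure, for every attack.
- For the between-arm compliance comparison and the two-year trend, use repeat attacks only and report unsupervised tablets taken over unsupervised tablets due. Give the number of missed intakes or missed days alongside, because a home-only share weights one missed intake more heavily on Coarsucam.
- Define tablets taken as the number handed out at D0 minus the number returned at D3, with a stated rule for vomited and re-administered doses. Record the number handed out for each attack on the CRF. Section 9.5 requires records of product issued and returned, but the accountability entries listed in section 9.2.2 do not include tablet counts.
- Reconcile the Coartem pack in section 9.3 with the 6, 12, 18 or 24 tablets per course implied by section 9.1, so that residual counts are read against the course and not the pack.

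The cost is a redefined numerator and denominator and one extra recorded count per attack; the D3 count is already planned. Reported compliance will be lower in both arms whenever home doses are missed, and each missed Coarsucam intake will weigh more.

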### Analysis of efficacy variables

The efficacy data analysis will be performed on the ITT population and on the Per Protocol population.

#### Analysis of primary efficacy variable(s)

The main criterion is defined as the response to the treatment after PCR correction according to WHO guidelines 2003 for the first attack.

The response will be classified such as:

- ETF (Early Treatment Failure)
- LPF ( Late Parasitological Failure)
- LCF (Late Clinical Failure)
- ACPR (Adequate Clinical and Parasitological Response)

The proportion of successes will be compared by group of treatment.

The main analysis is strictly defined as the non-inferiority analysis for the first attack.

The test of non inferiority between Coarsucam® group and Coartem® group will be based on the confidence interval method: the lower limit of the 95% one-sided confidence interval for the proportion difference between the two treatment groups should be greater than - to conclude non-inferiority.

#### Analysis of secondary efficacy variables

Non inferiority analysis will be performed on the same way than for the main criterion for

- before PCR corrected cure rate at D28 for the first attack
- before and after PCR corrected cure rate at D28 for the following attacks
- before and after PCR corrected cure rate at D42 for all attacks

An analysis for repeated measurements will be performed. A model will be built in order to explain the success/failure of the response. The rank of the attack, the group of treatment and their interaction will be included in the model. Some other relevant parameters could be included if descriptive analysis find out discriminating items.

Comparison between treatment groups will be provided for the following parameters

- Time to parasitological clearance for the 1st episode (number of patients without parasite from D1 to D3)
- Time to fever clearance for the 1st episode (number of patients without temperature from D1 to D3)
- Proportion of patients without fever at D3 for repeated attacks
- Proportion of patients without parasite at D3 for repeated attacks
- Evolution of number of gametocyte carriers and mean values of gametocyte rate during the 42 days of follow-up for each episode
- Evolution of hemoglobin value for each patient during each attack (between D0 and D28) occurring during the 2 years of follow up
- Evolution of mean hemoglobin values at D0,D3, D7,D14 and D28 of each episode during the 2 years of follow up
- Evolution of Hackett score during the 2 years of follow up

The number of malaria attacks will be summarized by treatment group and overall.

The evolution of average duration between 2 attacks during the 2 years of follow up will be computed and analyzed using survival analysis methods.

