### Management of treatment failures

Patients treated for uncomplicated malaria that are classified as failures (within 14 days of treatment) will be treated with quinine (10 mg/kg TID x 7d). In the unlikely event that a patient fails to have an adequate clinical response to quinine (either as first-line therapy for complicated disease or second-line therapy), treatment will be repeated with quinine (3 days) and clindamycin (5 mg/kg QID for 7 days). In this case, a failure CRF will be completed and patient will be followed-up until D42 from the initial enrolment Safety medication will be recorded in the failure case report form.

In experience of the site, failure to respond to quinine therapy is generally an indication of non-compliance. In the very unlikely event that a patient fails to have an adequate clinical response to quinine plus clindamycin therapy or if they develop severe or complicated malaria, they will be referred to Nagongera Health Centre IV or Tororo Hospital for further evaluation.

Treatment failures occurring on D14 or later have to be considering as reinfections and have to be treated with the same ACT allocated by the randomisation.

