### Secondary criteria

For the first episode:

- Clinical and parasitological efficacy is defined by grading clinical signs further to an interview by the investigator, together with the values obtained for temperature and parasitaemia before and after PCR correction at D42, and before PCR correction at D28
- Monitoring of parasitaemia during the different visits in order to define clearance
- Measure of axillary temperature at each visit in order to define the clearance of fever
- Monitoring of gametocytaemia during each evaluation

For the following episodes:

- Clinical and parasitological effectiveness is defined by grading the clinical signs further to an interview by the investigator, together with the values obtained for temperature and parasitaemia before and after PCR correction at D28 and D42
- Proportion of patients without fever at D3 obtained with the values of temperature (axillary temperature<37.5°C)
- Proportion of patients without parasites at D3 (negative thick smear)

During the total follow up of the cohort:

- Compare the number of malaria attack for each patient between two arms and mean delay between 2 attacks during the 2-years of follow up
- Compare the number of patients with anemia at D0 of each episode during the 2 years per arm.
- Compare the evolution of anaemia by patient between D0 and D28 for each episode

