#### Secondary efficacy variables

Comparison of both treatment groups in terms of:

- Response to treatment at D28, before PCR correction for the first attack
- Response to treatment at D28, before and after PCR correction for all repeated attacks
- Response to treatment at D42, before and after PCR for each attack
- Time to parasite clearance (proportion of aparasitaemic patients at 24, 48 and 72 hours) for the first attack
- Time to fever clearance (proportion of afebrile patients at 24, 48 and 72 hours) for the first attack
- Proportion of afebrile patients at D3 for the following attacks
- Proportion of patients without parasite at D3 for the following attacks
- Evolution of number of gametocytes carriers during the 42 days of follow-up and for each episode
- Evolution of the mean of gametocytes during the 42 days of follow-up and for each episode
- Evolution of abnormal biological baseline value for each attack
- Number of malaria attacks during the 2 years of follow up (treatment density)
- Evolution of the average duration between 2 attacks during the 2 years of follow up
- Evolution of haemoglobin value for each patient during each attack (between D0 and D28) during the 2 years of follow up
- Evolution of mean haemoglobin values at D0,D3, D7,D14 and D28 for each episode during the 2 years of follow up
- Evolution of Hackett score during the 2 years of follow-up

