## Statistical methods

All statistical analyses will be performed on SAS software (version 8.2 for PC).

All statistical tests will be performed at a 5% significance level and will be bilateral except for the non-inferiority analysis (unilateral confidence interval).

Distributions of parameters will be summarized by mean, standard deviation, median, minimum and maximum. These distributions will be compared using the Student t-test if normal distribution hypothesis is confirmed. Otherwise, distributions will be compared using the non-parametric Wilcoxon test.

All qualitative parameters will be summarized in contingency tables displaying frequencies and corresponding percentages.

For these parameters, a chi-square test (replaced by Fisher exact test if the expected frequency in any one of the cells of the contingency table is < 5) will be performed.

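### First-attack gametocyte carriage is compared without using D0 gametocyte status, which loses power but does not bias, and no cut-off is set for smears after quinine rescue

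*Protocol*

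**What the plan says.** Evolution of gametocyte carriage is a secondary objective for first and repeat attacks (Sections 6.2 and 10.1.2). Section 14.3.2.2 defines the variable as "Evolution of number of gametocytes carriers during the 42 days of follow-up and for each episode", with mean gametocyte values alongside. Section 14.5.3.2 makes it a comparison between arms: "Evolution of number of gametocyte carriers and mean values of gametocyte rate during the 42 days of follow-up for each episode".

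The general rules then apply:

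- **Population (14.5.3):** "The efficacy data analysis will be performed on the ITT population and on the Per Protocol population".
- **Level (14.5):** "All statistical tests will be performed at a 5% significance level and will be bilateral", with an exception only for the non-inferiority analysis.
- **Test for qualitative parameters (14.5):** "a chi-square test (replaced by Fisher exact test if the expected frequency in any one of the cells" has an expected frequency below 5. No stratification or adjustment is named.

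Measurement is complete. Section 10.1.2 provides for "Monitoring of gametocytaemia during each evaluation", and Section 10.1.3 schedules smears from D0 to D42 with gametocyte density read from the thick smear.

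Further treatment inside the 42 days is handled in two ways. Failures before D14 receive quinine; Section 9.7.4 says the "patient will be followed-up until D42 from the initial enrolment", and Section 12.1.2 has the CRF completed to D42 once quinine is prescribed. Failures at D14 or later are regarded as reinfections and "have to be treated with the same ACT allocated by the randomisation"; under Section 7.2 this starts a new 42-day follow-up.

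**The concern.** A child carrying gametocytes at D7 or D14 may have carried them at D0 and not cleared them, or may have been free of them at D0 and acquired them since. Drugs can act on either. D0 status is a strong predictor of later carriage, it is known for every child, and in the first attack it is measured before treatment. An unadjusted test leaves the variation due to D0 status in the error term.

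The second issue is the window. A smear taken after quinine reflects quinine as well as the study drug. It is collected inside the same episode, and the protocol does not say whether it counts. For adverse events Section 11.1 does end an episode's follow-up at re-treatment with study medication; there is no matching rule for gametocytes.

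At stake is a secondary comparison that could miss a real difference between the drugs. The primary analysis is untouched.

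**Working it through.** **Inputs.** From the protocol: two-sided 5% test, chi-square, two arms. The protocol gives no rate, effect size or power for gametocytes, so there is no stated figure to reproduce. Assumed: 190 evaluable children per arm in the first attack (200 are randomised), a share q of D0 carriers of 5, 15 or 30%, and a single post-baseline visit. Persistence in D0 carriers is r; new carriage in D0-negative children is v.

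**Crude rate in an arm:** p = q·r + (1−q)·v.

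**One case by hand.** Take q = 0.15, r = 0.60 in both arms, v = 0.02 against 0.08.

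- Crude rates: 0.15×0.6 + 0.85×0.02 = 0.107, and 0.15×0.6 + 0.85×0.08 = 0.158. The difference is 0.051.
- Unadjusted variance at the mean rate: 0.1325×0.8675 = 0.1149. Standard error: √(2×0.1149/190) = 0.0348. Then 0.051/0.0348 = 1.47 and power = Φ(1.47−1.96) = 31%.
- Variance within D0 strata: 0.85×0.05×0.95 + 0.15×0.6×0.4 = 0.0764. Standard error: √(2×0.0764/190) = 0.0284. Then 0.051/0.0284 = 1.80 and power = Φ(1.80−1.96) = 44%.

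The children and the difference are the same; only the error term is smaller.

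**All cases.** Crude and subset powers are by exact enumeration of the chi-square test. Mantel-Haenszel power is by simulation (200,000 runs, no continuity correction). Each cell gives q = 5 / 15 / 30%.

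| Assumed difference between drugs | Crude | Mantel-Haenszel by D0 status | D0-negative only | D0-positive only |
|---|---|---|---|---|
| New carriage only (2% v 8%; persistence 60% in both) | 56 / 31 / 17% | 66 / 44 / 24% | 78 / 73 / 64% | – |
| Clearance only (persistence 30% v 60%; new carriage 3% in both) | 10 / 33 / 68% | 11 / 42 / 82% | – | 25 / 61 / 90% |
| Both (2% v 8% and 30% v 60%) | 81 / 86 / 94% | 85 / 93 / 98% | 78 / 73 / 64% | 25 / 61 / 90% |

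The stratified test beats the crude test in all nine cases. With no difference between arms it rejects in about 5% of runs. Neither subset test wins throughout: when one drug is better on both effects, each has less power than the crude test.

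**Smears after rescue.** If a share f of an arm has had further treatment, with carriage c₀ without it and c₁ after it, observed carriage is (1−f)·c₀ + f·c₁. The spurious difference between arms is the difference in f times (c₀−c₁). Assume c₀ = 10% and c₁ = 4%:

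- f of 20% against 40%: 0.8×10 + 0.2×4 = 8.8%, against 0.6×10 + 0.4×4 = 7.6%. The false difference is 1.2 points.
- f differing by only 3 points, the size of the day-28 failure rate behind the sample size (about 2.7%): 0.03×6 = 0.18 points.

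Quinine before D14 alone is therefore likely to shift the comparison little. A large shift would need smears after ACT re-treatment to be kept in the earlier episode as well, which the protocol does not state.

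**The case against.** Four points have weight.

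1. **Bias.** A reader might infer that pooling D0 carriers with D0-negative children biases the comparison. It does not. In the first attack D0 status precedes treatment and is balanced in expectation, and total carriage is a legitimate target: the objective is carriage, not new carriage. The bullet also describes a course over visits, so D0 carriage would be visible. What remains is lost precision.

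2. **Smears after ACT re-treatment.** A reader might infer that they stay in the first attack's curve and that the comparison after D14 partly measures how often each arm was re-treated. That rests on silence. Sections 7.2 and 9.7.4 open a new episode, and the comparison is made for each episode, so those smears can belong to the new one alone. Section 9.7.1 also ends the active follow-up when a prohibited antimalarial is taken. Only the quinine smears are expressly collected to D42 of the same episode.

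3. **Subset tests.** Replacing the comparison by separate tests in D0-negative and D0-positive children is attractive only if the drugs differ on a single effect. With about 10 D0 carriers per arm, the protocol's own switch to Fisher's test also cuts the 25% power for persistence to 12%. From the second attack on, D0 carriage may depend on the drug given earlier, so such a split is no longer a randomised comparison.

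4. **Level of detail.** Baseline stratification of a secondary variable is often settled in the SAP, which is not shown and may already deal with it. But Section 14.5 does name an unadjusted test for all qualitative parameters, and Section 14.1 makes Section 14 the basis of the SAP. The point is therefore about a stated choice that can be improved, not about a missing detail.

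**Conclusion.** The point holds as a costless improvement to a secondary analysis. For the first attack, the unadjusted test is valid but gives up power that a test stratified by D0 gametocyte status would recover. At the assumed rates the gain runs from 1 point (10% to 11%) to 14 points (68% to 82%), and the stratified test is never worse in the cases examined. The size is illustrative: 190 per arm and every carriage, persistence and new-carriage rate are assumptions.

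The missing cut-off is real for smears after quinine rescue. Its effect is probably small, but it should be settled before the data are seen. The documents support neither a finding of bias nor one that smears after ACT re-treatment contaminate the first episode.

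**What to change.** In Section 14.5.3.2, or in the SAP:

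- **First attack:** compare carriage between arms with a Mantel-Haenszel test stratified by D0 gametocyte status (present or absent). Show new carriage in D0-negative children and persistence in D0-positive children as supporting descriptive results.
- **Cut-off:** within an episode, use gametocyte readings only up to the day a further antimalarial is given. Assign smears after ACT re-treatment at D14 or later to the new episode only. Report the number of children contributing at each visit, since the cut-off may remove more children from one arm.
- **Attacks 2 onward:** label any split by D0 status as non-randomised and descriptive, because D0 carriage may reflect earlier study treatment.

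The cost is wording and a few lines of programming. All data are already collected; no visit, sample or treatment rule changes.

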#### Laboratory variables analysis

Biological parameters will be summarized by group of treatment and overall at each time of measurement.

All abnormal variables will be graded and each parameter will be counted by grade.

The number of patients with abnormal data will be compared by grade between each treatment group and over the 2 years of follow-up

Transition tables will be provided between D0, D7 and D28 in order to assess the evolution of these parameters classified as normal/abnormal and by grade according to the laboratory ranges.

Absolute and relative changes to the baseline will be computed for each parameter for each attack. The evolution between D0 and D7 and D0 and D28 will be analyzed for each attack

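### Under the general rule in Section 14.5, the between-arm comparison of D0–D28 haemoglobin change ignores the D0 value and loses precision that baseline adjustment would recover at no cost

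*Protocol*

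**What the plan says.** Section 14.5.3.2 lists the variables on which the arms will be compared. One is "Evolution of hemoglobin value for each patient during each attack (between D0 and D28) occurring during the 2 years of follow up". Section 10.1.2 has the matching criterion: "Compare the evolution of anaemia by patient between D0 and D28 for each episode". Neither place names a test.

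The method comes from the general rule in Section 14.5. For continuous variables, "These distributions will be compared using the Student t-test if normal distribution hypothesis is confirmed". Failing that, "Otherwise, distributions will be compared using the non-parametric Wilcoxon test". On level and sidedness, "All statistical tests will be performed at a 5% significance level and will be bilateral except for the non-inferiority analysis". The only model with explanatory terms, in 14.5.3.2, is for treatment success or failure. It does not cover haemoglobin or laboratory values.

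For the laboratory parameters, Section 14.5.4.2 says "Absolute and relative changes to the baseline will be computed for each parameter for each attack" and "The evolution between D0 and D7 and D0 and D28 will be analyzed for each attack". It names no test and no between-arm contrast on those changes. The between-arm comparison it does state is on counts: "The number of patients with abnormal data will be compared by grade between each treatment group and over the 2 years of follow-up".

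Section 14.1 makes Section 14 the basis of the statistical analysis plan, which is to be finalised before database lock.

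**The concern.** Every child has a D0 haemoglobin, taken during an acute attack. Change from such a value can be expected to depend on the value itself: a child who starts low tends to rise more. Section 9.7.2 adds to this by giving iron to children with haemoglobin below 10 g/dL, so management after D0 also depends on D0. A two-sample test on the change makes no use of this dependence.

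Two things are at stake. The comparison serving the anaemia objective carries avoidable noise. And if the arms differ at D0 by chance at the first attack, part of that difference appears in the change score. The primary endpoint, PCR-corrected response at D28 of the first attack, has no baseline value and is not touched.

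**Working it through.** **Inputs.** The protocol gives no standard deviation, target difference, power or D0–D28 correlation for haemoglobin, so there is no stated figure to reproduce. From Section 14.2: 174 evaluable patients per arm. From Section 14.5: two-sided 5%. Assumed: a common standard deviation s at D0 and D28, and a correlation rho of 0.3, 0.5 or 0.7. Evolution is read as D28 minus D0.

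**Precision.** Per patient:

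- variance of the change score: 2(1 − rho)s²
- residual variance after adjusting D28 for D0: (1 − rho²)s²
- ratio, adjusted to change score: (1 − rho²) / [2(1 − rho)] = (1 + rho)/2

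This gives 1.3/2 = 0.65, 1.5/2 = 0.75 and 1.7/2 = 0.85.

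**Power.** At 80% power and two-sided 5%, the standardised effect is 1.96 + 0.84 = 2.80. Adjustment divides it by the square root of the ratio, so power is Φ(2.80/√ratio − 1.96). In the other direction, where the adjusted analysis has 80% power, the change-score test has Φ(2.80 × √ratio − 1.96). Detectable differences in units of s, at 80% power and 174 per arm, are 2.80 × √(2v/174), with v = 2(1 − rho) for the change score and 1 − rho² for the adjusted analysis.

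| Assumed rho | Variance ratio | Adjusted power where change score has 80% | Change-score power where adjusted has 80% | Detectable difference, change score → adjusted |
|---|---|---|---|---|
| 0.3 | 0.65 | 93.5% | 62% | 0.355 → 0.287 |
| 0.5 | 0.75 | 89.9% | 68% | 0.300 → 0.260 |
| 0.7 | 0.85 | 86.0% | 73% | 0.233 → 0.215 |

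The gain shrinks as rho rises: at rho = 0.8 the ratio is 0.90, and the change-score test has 76% power where the adjusted analysis has 80%.

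**Effect of a chance imbalance, first attack only.** Over all randomisations the change-score test is unbiased with type I error 5%. Given a D0 difference of k standard errors, the test statistic shifts by k × √((1 − rho)/2) in the opposite direction, that is 0.59, 0.50 and 0.39 per standard error at the three values of rho. Its conditional standard deviation is √((1 + rho)/2). Conditional type I error is then:

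- k = 1: 4.6%, 4.8% and 5.0%
- k = 1.96: 16%, 13% and 10%

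The distortion matters only when the chance imbalance is large.

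**The case against.** The strongest reply is that covariates for secondary and safety variables are usually set in the statistical analysis plan, which is not shown, and that nothing in the protocol forbids adjustment. That is true, and it limits the weight of the point. It does not remove it: Section 14.5 is not silent but sets an unadjusted default, Section 14.1 makes it the basis of the later plan, and 14.5.3.2 offers nothing else for haemoglobin.

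Three stronger readings are tempting, and the document does not support them.

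- A reader might infer that the laboratory changes are also compared between arms by t-test. Section 14.5.4.2 does not say so. Section 10.2.3 implies some between-arm comparison of biological parameters, with the episode as unit, but names neither the variable nor the test. The laboratory part is therefore conditional.
- A reader might infer that the haemoglobin comparison is biased. At the first attack it is not, over randomisation: the change score already subtracts D0. Only the conditional shift computed above remains.
- A reader might infer that each attack's own D0 should be a covariate. From the second attack on, D0 is measured after randomisation and may reflect earlier study treatment. Section 10.1.2 makes the number of children anaemic at D0 of each episode a criterion in its own right. Conditioning on it could remove part of the cumulative effect sought under the anaemia and repeated-treatment objectives in Section 6.2.

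It is also fair to say that the size rests on an assumed correlation and a hypothetical 80% starting power.

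**Conclusion.** The point holds for haemoglobin. Applied as written, the general rule gives an unadjusted D0–D28 comparison whose variance is larger than necessary: the adjusted analysis has 65% to 85% of it for rho between 0.3 and 0.7. In power terms the gain is about 6 to 13.5 points from a starting value of 80%. This rests on the assumed correlation, equal standard deviations at D0 and D28, and reading evolution as the change score. The exposure to chance imbalance is conditional, confined to the first attack, and small unless the imbalance is large.

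This is a modest efficiency point on a secondary comparison. It does not affect the primary non-inferiority conclusion.

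**What to change.** In Section 14.5.3.2, and in the statistical analysis plan, state:

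- **First attack, haemoglobin:** compare D28 haemoglobin between arms by analysis of covariance with D0 haemoglobin and age as covariates. Keep the t-test or Wilcoxon results as descriptive.
- **First attack, laboratory values:** say in 14.5.4.2 whether the arms are compared on D7 and D28 values. If so, use the same model, on the log scale where the parameter is skewed (ALT, bilirubin and neutrophils are likely candidates). This would also settle the choice between absolute and relative change, both of which are computed with neither given priority.
- **Repeat attacks:** use a mixed model with child as random effect, adjusted for the first-attack D0 value and not for the D0 of the current attack.

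The cost is a few sentences. The D0, D7 and D28 measurements are already scheduled. Section 14.1 allows the plan to be revised on blinded review, so the wording can be fixed before database lock.
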